### Recruitment and Sampling

Due to the institutional data protection constraints, it is not possible to distribute the survey invitation directly to all university employees. Consequently, a multichannel recruitment strategy is being implemented. The study information sheet and participation link are being disseminated via email to deans, faculties, departments, and the human resources department of the UAH, who may forward it to relevant bodies at their discretion. In addition, posters containing QR codes and brief study details are placed on bulletin boards across UAH buildings to increase visibility. Participants are also encouraged to share the study with colleagues to broaden its reach and improve participation rates, thereby introducing a secondary snowball component.

While this strategy incorporates elements of exponential snowball sampling, it is designed to promote broad participation across different occupational roles while complying with data protection policies. This approach facilitates access to diverse occupational profiles and enhances heterogeneity in the study sample.

### Sample Size

The sample size was calculated for a finite population using Microsoft Excel based on the total UAH workforce (N=3117). A minimum of 796 (25.53%) participants were required to achieve a 95% CI, 3% margin of error, and population proportion of 0.5. This last value was chosen due to the absence of previous prevalence data on the variables of interest, as it maximizes sample size under conditions of uncertainty and ensures sufficient statistical power across all outcomes. Accounting for a potential 10% dropout rate, the final estimated sample size was determined to be 885 (28.39%) participants.

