### Objectives

On the basis of the aforementioned background, the primary objective of this study is to analyze the relationship between LTPA and work ability among university staff in the CAM, considering the potential modifying effect of OPA, and exploring differences by sex and gender. The secondary objectives are to (1) determine the prevalence of MSDs in this population and analyze their association with LTPA and OPA levels using validated questionnaires; (2) evaluate the relationship between both domains of PA and perceived physical and mental workload, adjusting for occupational role and sociodemographic factors; (3) examine the association between LTPA and OPA and self-perceived health-related quality of life (HRQoL); and (4) explore whether these associations vary according to sex, gender, and occupational category.

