### Study Population and Setting

The study population consists of university staff working in the CAM. A representative sample of 885 workers from the University of Alcalá (UAH), Alcalá de Henares, Madrid, Spain, was selected. Participants include members of the PTGAS, PDI, and PI.

Inclusion criteria are (1) aged ≥18 years and (2) having sufficient proficiency in Spanish to complete study procedures. The questionnaire will be administered exclusively in Spanish, as it is the official and working language in the study setting. Consequently, only participants with adequate Spanish comprehension will be eligible. While this approach ensures the reliability of self-reported data, it may limit the generalizability of the findings to non–Spanish-speaking university staff.

Exclusion criteria include (1) cognitive impairment preventing comprehension of study information or completion of the survey, (2) severe neurological deterioration, and (3) diagnosed severe mental illness preventing the provision of informed consent.

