### Strengths and Limitations

This protocol presents several strengths. First, it uses validated and widely used instruments to assess LTPA, OPA, work ability, and relevant covariates, alongside comprehensive sociodemographic data. The online, self-administered format of the questionnaire reduces potential bias associated with interviewer-led responses and facilitates participation across diverse occupational groups. By collecting key covariates, this study is designed to account for potential confounding factors, ensuring that observed associations are more likely attributable to the primary research objectives. In addition, the estimated sample size provides adequate statistical power to detect significant associations, and the inclusion of participants with varied occupations and occupational demands enhances the generalizability of findings to the broader CAM working population.

The primary limitation of this study is its cross-sectional design, which precludes causal inference between the variables of interest. Longitudinal and interventional studies will be necessary to establish causal relationships and evaluate the effectiveness of tailored PA interventions. In addition, the use of a nonprobability sampling strategy, necessitated by institutional data protection constraints, may introduce selection bias and limit representativeness. However, the multichannel recruitment approach has been carefully designed to promote broad dissemination across occupational groups, and the anticipated heterogeneity of the sample is considered sufficient for the study’s exploratory objectives. Moreover, the use of self-reported measures introduces the possibility of reporting bias, which could affect the accuracy of certain variables. Nevertheless, the use of validated instruments mitigates this concern to some extent. Finally, the absence of objective PA measurements (eg, accelerometers or step counters) may limit the precision of exposure assessment; however, this was a deliberate decision made during the study design phase to prioritize anonymity and feasibility, and it will be addressed in future phases involving subsamples with identifiable data.

As all questionnaire items are mandatory, missing data are not expected. Nonetheless, any unexpected data loss (eg, due to technical issues) will be managed using listwise deletion.

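### The ±3% margin behind the sample size of 796 (885) is worked out for the 3117 UAH staff, but the stated study population is university staff in the CAM, for which that finite-population correction is not valid

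*Protocol article*

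**What the plan says.** The Sample Size section bases the calculation on one university: "The sample size was calculated for a finite population using Microsoft Excel based on the total UAH workforce (N=3117"). It continues: "A minimum of 796 (25.53%) participants were required to achieve a 95% CI, 3% margin of error, and population proportion of 0.5". It then allows for loss: "Accounting for a potential 10% dropout rate, the final estimated sample size was determined to be 885 (28.39%) participants".

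The population is described more widely elsewhere. The primary objective is to "analyze the relationship between LTPA and work ability among university staff in the CAM". Study Population and Setting opens with "The study population consists of university staff working in the CAM" and goes on: "A representative sample of 885 workers from the University of Alcalá (UAH), Alcalá de Henares, Madrid, Spain, was selected". Strengths and Limitations says that the variety of occupations in the sample "enhances the generalizability of findings to the broader CAM working population".

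The article gives no total for university staff in the CAM. Recruitment and Sampling describes channels at UAH only, plus onward sharing among colleagues. Strengths and Limitations acknowledges that the sampling is not probability-based.

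**The concern.** A finite-population correction shrinks the margin of error because a known, sizeable share of the target population has been observed. Here that share is about a quarter, and it is a quarter of UAH. If the target is all university staff in the CAM, the share is smaller by an unknown amount and the reduction is too large.

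The ±3% is the only precision figure in the article. Nothing in the text limits it to UAH, and the sentence calling the sample representative directly follows the one naming CAM staff as the population. The first secondary objective is a prevalence of musculoskeletal disorders in that population, which is the kind of quantity a margin of error describes. A reader could therefore take ±3% as the precision for CAM university staff.

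**Working it through.** **Inputs from the Sample Size section:** N = 3117, p = 0.5, margin e = 0.03, 95% confidence (z = 1.96), dropout 10%. **Not in the document:** the number of university staff in the CAM. It is treated as an assumption and varied below.

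**1. Reproducing the plan's figures.**
- Uncorrected size: n0 = z²p(1−p)/e² = 1.96² × 0.25 / 0.0009 = 1067.1, rounded up to 1068.
- Corrected size: n = n0 / (1 + (n0 − 1)/N) = 1067.1 / (1 + 1066.1/3117) = 795.1, rounded up to 796. This matches.
- Dropout: 796 / 0.9 = 884.4, rounded up to 885. This matches.

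The correction alone takes the requirement from 1068 to 796.

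**2. Margin for the UAH workforce.** Margin = z√(p(1−p)/n) × √((N−n)/(N−1)).
- n = 796: 3.47% × √(2321/3116) = 3.47% × 0.863 = 3.00%.
- n = 885: 3.29% × √(2232/3116) = 3.29% × 0.846 = 2.79%.

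The stated 3% is right for these 3117 people, given simple random sampling and an interval computed with the same correction.

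**3. Margin without the UAH correction.**
- n = 796: 1.96 × √(0.25/796) = 3.47%.
- n = 885: 1.96 × √(0.25/885) = 3.29%.

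These are upper limits, reached when the population is very large. The planned 10% loss takes 885 to 885 × 0.9 = 796.5, so the figure at 796 is the relevant one for planning.

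**4. Range over assumed CAM totals**, using the formulas of steps 1 and 2 with the assumed total in place of 3117:

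| Assumed CAM total | Margin at 796 | Margin at 885 | Completers needed for ±3% |
|---|---|---|---|
| 5,000 | 3.19% | 2.99% | 880 |
| 10,000 | 3.33% | 3.15% | 965 |
| 20,000 | 3.40% | 3.22% | 1014 |
| 50,000 | 3.45% | 3.26% | 1045 |
| No limit | 3.47% | 3.29% | 1068 |

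The lowest assumed total is a generous one: UAH would then make up 3117/5000 = 62% of all CAM university staff. At 796 completers every assumed total gives more than 3%, so the direction does not depend on the assumption. The excess is between about 0.2 and 0.5 percentage points.

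**5. What these figures do not show.** Every row treats the respondents as a simple random sample of all CAM university staff. They come from one university by a non-probability route. Differences between universities do not enter z√(p(1−p)/n), so the table shows nominal margins, not true margins for the CAM.

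**The case against.** The strongest reply is that nothing has been miscalculated. The section names the UAH workforce as its basis, the next section but one before it says the 885 come from UAH, and recruitment runs through UAH channels. On this view UAH is the accessible population, the CAM is the setting, and 3117 is the correct N for the people sampled. Dropping the correction would also not help: a one-university sample has no known selection probabilities for staff elsewhere in the CAM, so ±3.5% would be no truer for the CAM than ±3%.

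Much of this stands. The figures 796 and 885 are correct for UAH, and a restated CAM margin can only be nominal. What does not stand is that the text already settles the matter. The study population and the primary objective are stated for the CAM, the generalisation goes wider still, and neither the ±3% nor the conclusions are limited to UAH. The acknowledged limitation concerns how respondents are selected. The mismatch in N would remain even with a perfect random sample of UAH staff.

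Two stronger readings are tempting and are not supported. A reader might infer that the true margin is 3.5%; that is the limit for an unlimited population, and the document gives no CAM total. A reader might also infer that the study will report intervals with too little coverage: a ±3% interval at 796 without the correction would nominally cover 2Φ(0.03/0.01772) − 1, about 91%. The article plans no such interval. Planned Data Analysis promises 95% confidence intervals for regression coefficients and does not mention a finite-population correction.

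**Conclusion.** The point holds as an inconsistency between the population in the formula and the population in the objectives, not as a calculation error. The ±3% is valid for the UAH workforce under simple random sampling. It does not carry over to university staff in the CAM, where the nominal margin at 796 completers is at most ±3.47%, or about ±3.2% to ±3.5% for assumed totals from 5,000 upward. The figure of ±3.29% needs all 885 to complete, and ±3% needs up to 1068 completers.

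The numerical effect is modest, at most about half a percentage point. It bears on prevalence estimates. The primary objective concerns an association, which this margin does not describe. The point still merits correction because it affects the only precision figure given and the repair is cheap.

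**What to change.** **Preferred.** In Sample Size, state that the ±3% margin refers to the UAH workforce of 3117 only, and that it holds only if prevalence intervals are computed with the same correction. Align the target population in Objectives and in Study Population and Setting with UAH, and narrow the generalisation in Strengths and Limitations to match. The objective in the Abstract needs the same change.

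**If the CAM target is kept.** Drop the correction and restate the margin as nominally up to about ±3.5% at 796 completers, noting that ±3% would correspond to up to 1068. Add that a non-probability sample from one university does not deliver a true margin for the CAM.

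Either way the change is a few sentences, needs no extra recruitment and can be made while data collection continues. The cost is a narrower stated population in the first case and a slightly less favourable figure in the second.

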#### Primary Variables

The primary variables include LTPA, OPA, and work ability. LTPA and OPA are assessed using the Spanish version of the Global Physical Activity Questionnaire [41]. This tool assesses PA in 3 domains: occupational, active transport, and leisure, yielding weekly metabolic equivalent of task (MET) minutes for each. MET minutes are calculated by multiplying activity duration by the standard MET values.

The official Spanish version of the questionnaire, endorsed by the WHO, has shown good test-retest reliability (intraclass correlation coefficient=0.70-0.90) and moderate concurrent validity (Spearman ρ≈0.42) compared with the accelerometry in European and Latin American Spanish-speaking populations. Although it has not been formally validated in Spain, its widespread international use and standardization support its inclusion in this study [42].

Work ability is being assessed with the Spanish version of the Work Ability Index (WAI) [43]. The WAI measures 7 dimensions: current work ability compared to lifetime best, work ability in relation to job demands, physician-diagnosed illnesses, estimated work impairment due to illness, sick leave over the past year, prognosis of work ability over the next 2 years, and mental resources. Total scores classify work ability into 4 categories: poor (7-27), moderate (28-36), good (37-43), and excellent (43,45-49). The WAI has been adapted and endorsed by the Spanish National Institute for Safety and Health at Work (NTP 1147) for the Spanish occupational context [43]. It was validated in a sample of 1184 Spanish health center workers, demonstrating satisfactory reliability (intraclass correlation coefficient>0.75), a stable 2-factor structure, and convergent validity with measures of health and productivity, reflecting strong psychometric properties in occupational settings [44].

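### The sample size is a ±3% precision calculation for one proportion, so the claim that it secures power for all outcomes does not follow, and power for the moderation analyses is not shown

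*Protocol article*

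**What the plan says.** In the protocol article, Sample Size, the calculation is set up to "achieve a 95% CI, 3% margin of error, and population proportion of 0.5" in a workforce of 3117. The result: "A minimum of 796 (25.53%) participants were required". "Accounting for a potential 10% dropout rate", "the final estimated sample size was determined to be 885 (28.39%) participants". The value 0.5 is justified by the lack of earlier prevalence data, and the text adds that this choice "ensures sufficient statistical power across all outcomes".

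Strengths and Limitations returns to the point and lists as a strength that "the estimated sample size provides adequate statistical power to detect significant associations".

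The Objectives section makes the primary question the relationship between LTPA and work ability, with OPA as a possible modifier. Planned Data Analysis answers it with multiple linear and logistic regression, interaction terms, strata by sex, gender and job category, and a mediation analysis, all at P<.05. It also plans high/low groups for each activity domain, cut at 600 MET-minutes per week.

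**The concern.** Precision for a proportion and power for a regression coefficient are different properties. Setting p=0.5 maximises p(1−p), and so gives the largest sample for a given CI width. It fixes nothing about the chance of detecting a difference in Work Ability Index score, let alone a difference between differences.

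The claim is also universal, since it covers every outcome. Interactions and strata are where a sample that suffices for a main effect most often falls short. If the power statement stands, a null interaction or a null stratum is likely to be read as evidence that OPA, sex or gender does not modify the association, because the protocol promised enough power to see it.

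**Working it through.** **1. The plan's own figures.** Inputs from Sample Size: N=3117, z=1.96, margin 0.03, p=0.5, dropout 10%.

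- n₀ = 1.96² × 0.25 / 0.03² = 1067.1
- n = 3117 × 1067.1 / (3116 + 1067.1) = 795.1, rounded up to 796
- 796 / 0.9 = 884.4, rounded up to 885

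Both reproduce exactly from these five inputs alone. Nothing about effects, variances, exposure distribution or power was used.

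**2. Is p=0.5 conservative for power?** For a linear model of the Work Ability Index it is irrelevant. For a logistic model it is the favourable case. With four equal cells of 199, the SE of the log ratio of odds ratios is √(4 / [199 × p(1−p)]).

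- Prevalence 50%: SE = 0.284; detectable ratio = exp(2.80 × 0.284) ≈ 2.2
- Prevalence 20%: SE = 0.354; detectable ratio = exp(2.80 × 0.354) ≈ 2.7

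Power is therefore best at 50% prevalence, and planning at 0.5 does not protect outcomes with other prevalences.

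**3. Detectable effects for a continuous outcome.** The documents give no SD, effect size or exposure split, so the following are assumptions: binary high/low exposures independent of each other, 50% high LTPA, effects in SD units of the outcome, two-sided 5%, 80% power (1.96 + 0.84 = 2.80), n=796.

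- Main LTPA effect: 2.80 × √(1/398 + 1/398) = 0.20 SD
- LTPA×OPA interaction: 2.80 × √(sum of 1/cell size)

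| High OPA | Cell sizes (each twice) | Detectable interaction | Power at 0.20 SD | Power at 0.30 SD | Power at 0.50 SD |
|---|---|---|---|---|---|
| 50% | 199, 199 | 0.40 SD | 29% | 56% | 94% |
| 30% | 119, 279 | 0.43 SD | 25% | 49% | 90% |
| 20% | 80, 318 | 0.50 SD | 20% | 39% | 81% |
| 10% | 40, 358 | 0.66 SD | 13% | about 25% | 56% |

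If all 885 are analysed, the balanced case improves only to 0.38 SD, with 61% power at 0.30 SD. For 80% power in the balanced case, a 0.30 SD interaction needs 1396 participants and a 0.20 SD interaction needs 3140, which is more than the workforce of 3117.

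**4. Within one sex.** Take half the sample, n=398, and 50% high LTPA.

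- 30% high OPA: 2.80 × √(2/59.7 + 2/139.3) = 0.61 SD
- 15% high OPA: 2.80 × √(2/29.9 + 2/169.2) = 0.79 SD

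**5. Against the protocol's own hypothesis.** Anticipated Findings suggests that high OPA may weaken or cancel the LTPA benefit. If that benefit is 0.20 SD, about the smallest main effect detectable, and high OPA cancels it entirely, the interaction is 0.20 SD. The best power in the table for that is 29%, and partial weakening has less.

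**The case against.** The strongest reply is that inadequate power cannot be proved from this document. Without an effect size or an OPA split, a reader might infer from the table that the design is underpowered for its primary interaction. The documents do not support that as a fact: a 0.50 SD interaction has 81% power or more whenever at least 20% have high OPA. What can be said is that power is not shown, and that under these assumptions it falls short of 80% for interactions below about 0.40 SD even with balanced groups.

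The LTPA×OPA product term is also an inference. Planned Data Analysis names interaction terms for gender, and for occupational role with the activity levels, but not this one. That stands. However, the Objectives section puts OPA modification in the primary question, and the same 0.40 SD floor applies to a gender×LTPA term with even splits.

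The statement in Strengths and Limitations is narrower than the one in Sample Size. For the main LTPA association it is undocumented but plausible at about 0.20 SD or more, so it needs limiting and not deleting. The text already describes much of the sex, gender and subgroup work as exploratory and promises 95% CIs for all regression coefficients, which reduces the risk of misreading. None of this rescues the all-outcomes claim, which is an affirmative statement and not a detail left to an analysis plan.

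Two stronger readings should be resisted:

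- A reader might take the questionnaire's "moderate concurrent validity (Spearman ρ≈0.42) compared with the accelerometry" and infer a required sample 1/0.42² ≈ 5.7 times larger. That needs classical error, accelerometry as error-free truth, and the same correlation in the leisure and occupational domains. The protocol gives no domain for the figure, and the attenuation formula is for continuous exposures, not the high/low groups used here.
- A reader might infer that the sex analyses need interactions of 0.9 to 1.1 SD. That is a three-way contrast (twice the two-way values), which the protocol does not plan.

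**Conclusion.** The point holds in limited form. The sums for 796 and 885 are correct; the inference drawn from them is not. A precision calculation for one proportion cannot deliver power across all outcomes, and power for the regression, moderation and stratified analyses is not shown anywhere in the protocol.

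The size of the gap rests on the assumptions in the working. With those, the main LTPA effect is reasonably covered, while the interaction must be at least twice as large to be detected with the same power, and more than three times as large if only 10% have high OPA. The planned sample itself is not shown to be wrong.

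**What to change.** No change of n or of the analyses is needed.

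1. **Sample Size:** delete the clause on power. Describe 796 (885 with dropout) as the target for ±3% on a single proportion in the UAH workforce under simple random sampling. The recruitment described is not a probability sample, so that condition should be stated.
2. **Sample Size:** add a short paragraph with the smallest detectable LTPA main effect and LTPA×OPA interaction at the planned n, giving the SD units, assumed exposure splits, alpha and power.
3. **Strengths and Limitations:** limit the power statement to the main association between LTPA and work ability at about 0.20 SD or larger, under the stated assumptions. Add that null interaction, stratum and mediation results will be read from their 95% CIs and not as evidence of no modification or no mediation.

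The cost is some rewording and one paragraph of calculation, and the stated claim becomes less favourable. According to Results, recruitment is still open and no analyses have been run, so the correction can be made before any result is known.
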